### Biological specimens

Not applicable in this study.

### Data analysis

At the end of all measurements’ data collection, a skilled statistician blinded to group allocation will be performed by SPSS Statistics for Windows, version 22.0 (SPSSInc., Chicago, III., USA). We will descriptively summarize patient characteristics, outcome variables, and adverse events. Continuous variables, such as age and disease course, will be presented as mean ± standard deviation (*SD*) and analyzed by an independent-sample *T*-test. Quantitative variables such as baseline variables of socio-demographic data will be analyzed using *χ*^2^ or Mann-Whitney *U* tests. The repeated measurement variables, such as the primary and second outcomes, are analyzed by repeated-measures analysis of variance (ANOVA) or generalized estimation equations (GEE).

Both the full analysis set (FAS) and the per-protocol analysis set (PPS) will be used simultaneously to evaluate the effect and safety of GFW for PD. The FAS is for all participants who complete randomization and are assigned to receive treatment. The PPS is for the individuals who receive the assigned treatment according to the protocol and complete the entire study. For missing data, we will use the last-observation-carried-forward method. Although no interim analysis of outcomes is planned, a summary of the enrolment progress, AEs, and protocol deviations will be provided to the data monitoring committee (DMC) members. The trial should be terminated if there is clear evidence that SAEs are associated with the intervention or develop a serious illness. Statistical significance will be set at *P* < 0.05.

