
## Methods

### Design and setting

This study is a randomized, double-blind, and placebo-controlled exploratory trial with two parallel groups. The study is designed using Consolidated Standards of Reporting Trials guidelines Extension for Chinese Herbal Medicine Formulas 2017 (CONSORT CHM Formula) [20] and adhere to the Declaration of Helsinki (2013 version). Meanwhile, we designed the study according to the Standardized Protocol Items: Recommendations for Interventional Trials (SPIRIT) statement [23] (details see Additional file 1). The study protocol has been approved by the Ethical Committee of The Second People’s Hospital of Yichang (No. 2020001) and has been registered at the Chinese Clinical Trials Registry in 2020 (No. ChiCTR2000034118.) (details see https://trialsearch.who.int/Trial2.aspx?TrialID=ChiCTR2000034118 and Additional file 2).

The trial is being conducted at the Second People’s Hospital of Yichang. Participants meeting the inclusion criteria will be randomly allocated to either the GFW group (treated with GFW) or the control group (treated with a matching placebo) in a 1:1 ratio. The total observation period will be 7 months, including a 1-month baseline period, a 3-month treatment period, and a 3-month follow-up period. The intensity of menstrual pain and the acute medication use will be asked to record in dysmenorrhea diaries throughout the trial. Assessments will be conducted at baseline and at 1, 2, 3, 4, 5, and 6 months postmenstrual cycles. The flow chart is shown in Figs. 1 and 2 illustrates the schedule of enrolment, interventions, assessments, and data of participants.

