### Outcome measurements

The time points for all outcomes are at baseline and at 1, 2, 3, 4, 5, and 6 months postmenstrual cycles.

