#### Primary outcome

The primary outcome is the mean menstrual pain intensity change measured by visual analog scale (VAS) from baseline to 6 months. The VAS is a valid and reliable tool that has been widely used in various clinical trials involving patients with PD [27]. Participants will be asked to indicate a perception of pain intensity scored from 0 to 100 (0, no pain; 100, maximum).

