### Sample size

The sample size estimation was based on the mean difference in the change of the menstrual pain intensity from baseline. Based on previous studies and our pilot trial, we made the following assumptions in calculating the sample size: a mean difference of 1 between two groups, SD of total score of 1.67, a ratio of 1:1 between the two groups, a two-sided significance level of 0.025 and a power of 0.9 [35, 36]. With these assumptions, a minimum sample size of 116 patients (58 patients in each group) is needed. Considering an estimated 10% dropout rate, the estimated sample size was 128 patients (64 patients per group).

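### The primary analysis is left as repeated-measures ANOVA or GEE, with no selection rule and no named effect tied to the baseline-to-6-months endpoint

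*Protocol article*

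**What the plan says.** All places are in the protocol article, under Methods.

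- Primary outcome: "The primary outcome is the mean menstrual pain intensity change measured by visual analog scale (VAS) from baseline to 6 months".
- Sample size: "The sample size estimation was based on the mean difference in the change of the menstrual pain intensity from baseline", with "a mean difference of 1 between two groups" and "SD of total score of 1.67".
- Outcome measurements: "The time points for all outcomes are at baseline and at 1, 2, 3, 4, 5, and 6 months postmenstrual cycles". That makes seven assessments.
- Design and setting describes a 7-month observation period, "including a 1-month baseline period, a 3-month treatment period, and a 3-month follow-up period". Assessments 4, 5 and 6 therefore fall after treatment has ended.
- Data analysis: "The repeated measurement variables, such as the primary and second outcomes", "are analyzed by repeated-measures analysis of variance (ANOVA) or generalized estimation equations (GEE").

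Data analysis gives no rule for choosing between the two methods, no model terms, no covariates and no deciding effect. It also sets last observation carried forward for missing data and P < 0.05 for significance.

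**The concern.** The endpoint and the sample size both point to a single number, the between-group difference in VAS change. The analysis text points to a family of methods that produce several numbers. The usual outputs of a repeated-measures ANOVA are a group main effect averaged over the visits entered and an omnibus group-by-time test, which has 6 degrees of freedom if all seven assessments enter. Neither is the difference at month 6. GEE can be set up to give any of the three.

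With three treated and then three untreated assessments, an effect that appears on drug and fades afterwards is a plausible pattern. It is also a pattern in which the candidate tests disagree. If the deciding effect is not fixed in advance, the headline P value may answer a different question from the stated endpoint, and the choice could be made after the results are seen.

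**Working it through.** **Step 1. Reproduce the plan's sample size.** Inputs from Sample size: difference 1, SD 1.67, power 0.9, 1:1 allocation.

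n per group = 2 × SD² × (z_α + z_β)² / δ². At two-sided 0.05 this is 2 × 2.7889 × (1.960 + 1.282)² / 1 = 58.6, so 59. The plan states 58, for which power is Φ(1 / (1.67 × √(2/58)) − 1.960) = Φ(3.225 − 1.960) = 0.897. The plan's literal two-sided 0.025 gives 69.2, so 70, and does not reproduce its figure; that is a separate point. The stated size thus fits a two-sample comparison of one change score at two-sided 0.05.

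**Step 2. Assumptions for comparing the candidate tests.** 58 per group, two-sided 0.05, seven assessments all entered. The plan's 1.67 is taken as the SD of change, although the article calls it the SD of a total score. Variances are equal and every pair of visits has the same correlation ρ. The article gives no ρ, so 0.3, 0.5 and 0.7 are shown. The single-visit variance is then σ² = 1.67² / (2(1 − ρ)) = 1.992, 2.789 and 4.648.

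**Step 3. Effect on drug only.** Group differences at baseline and months 1 to 6 are 0, 1, 1, 1, 0, 0, 0.

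- Month-6 change: the true difference is 0, so the test rejects in 5% of trials.
- Group main effect: the mean difference is 3/7 = 0.429, with SE = √(σ² × (1 + 6ρ)/7 × 2/58) = 0.166, 0.234 and 0.345. The ratios 2.585, 1.828 and 1.242 give rejection rates of 0.73, 0.45 and 0.24. Simulation of 2,000 trials per case gave 0.72, 0.45 and 0.23.
- Group-by-time: the noncentrality is (58/2) × Σ(d − d̄)² / (σ²(1 − ρ)). The sum of squares is 1.714 and σ²(1 − ρ) = 1.67²/2 = 1.394 at every ρ, so the noncentrality is 35.65. On 6 and 684 degrees of freedom the test rejects in 0.998.

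**Step 4. Other effect patterns, same method** (ρ = 0.3 / 0.5 / 0.7).

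| Pattern | Month-6 change, unadjusted | Group main effect | Group-by-time |
|---|---|---|---|
| On drug only | 0.05 | 0.73 / 0.45 / 0.24 | 0.998 |
| 1 at months 1–3, fading to 0 at month 6 | 0.05 | 0.93 / 0.68 / 0.38 | 0.984 |
| Sustained at 1 | 0.897 | 0.999 / 0.955 / 0.700 | 0.905 |
| Rising linearly to 1 at month 6 | 0.897 | 0.855 / 0.569 / 0.305 | 0.870 |

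**Step 5. What baseline adjustment adds.** Relative to the change score, the variance of the adjusted month-6 comparison is multiplied by (1 + ρ)/2, a cut of (1 − ρ)/2 = 35%, 25% and 15%. The effective SD is 1.67 × √((1 + ρ)/2) = 1.35, 1.45 and 1.54. Power with 58 per group becomes 0.979, 0.961 and 0.938. The number needed for 90% power at two-sided 0.05 is 39, 44 and 50 per group; at two-sided 0.025 it is 45, 52 and 59. All are within the planned 64 per group.

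**The case against.** A reader might infer that the plan does not test its own endpoint. The article does not support that. Both methods can yield a month-6 group contrast; the text fails to name one but does not exclude it. That all seven visits enter the model is a fair inference from Outcome measurements, but Data analysis does not say so.

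A reader might also infer that the plan wrongly omits baseline adjustment. The article is silent on covariates, which are commonly left to the full protocol or SAP, and baseline could enter as one of the repeated measurements. Under randomisation an unadjusted comparison is valid and costs only precision.

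Nor can it be said that the plan would miss a real month-6 effect. With a sustained effect the interaction matches the unadjusted change score (0.905 against 0.897). Even if the effect appeared at month 6 alone, the interaction would keep power of about 0.9. A serious loss arises only if the main effect is made decisive. In the on-drug-only case a treatment effect does exist, so a significant omnibus test is not a false claim of any effect; it is an answer to another question.

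The endpoint sentence could also be read as change over the whole course to 6 months, which a group-by-time analysis would address. Month-6 change is the more natural reading and fits the sample size, but this ambiguity is a further reason to name the contrast.

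Finally, Design and setting calls the trial exploratory, and the statistician is blinded to allocation. Both lower the stakes. Blinding reduces the scope for a data-driven choice but does not remove it. What stands is that the article does state the primary method, and states it as an open pair with no deciding effect. That is more than detail left to another document.

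**Conclusion.** The point holds in a limited form: the primary method is open between two families, and no effect is tied to the VAS change from baseline to 6 months on which the trial is sized.

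The consequence depends on the pattern of effect. If it is confined to treatment, the interaction rejects in about 99.8% of trials and the main effect in 23 to 73% (calculation and simulation together), with no difference at month 6. If it is sustained, the interaction loses nothing, and among the correlations tried the main effect falls below the change score only at 0.7. These figures rest on the assumed correlations, equal variances, 1.67 as the SD of change, and all seven visits in the model.

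No figure stated in the article is wrong because of this point. Given the exploratory label and the blinded statistician, it is a recommended improvement and not a condition for the trial to be sound.

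**What to change.** Before unblinding, state one model and one primary test.

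- Model: for example, a mixed model for repeated measures on VAS at assessments 1 to 6, with treatment, visit, treatment-by-visit, baseline VAS and baseline-by-visit. GEE with the same named contrast would also be defensible; what matters is that one is chosen.
- Primary test: the baseline-adjusted between-group difference at month 6, with 95% CI, two-sided 0.05. If change over the whole course is meant instead, the endpoint sentence should say so and the contrast should follow it.
- Missing data: fit the model to observed data without last observation carried forward, and amend that rule for the primary analysis, since filled-in values do not belong in a likelihood-based model.
- Keep GEE as a sensitivity analysis.

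The cost is wording. Baseline VAS is already collected, no visits or patients are added, and the planned 64 per group is enough under the assumptions above. The article reports that recruitment was ongoing at submission.

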Participants are free to withdraw from the trial if they feel they are not getting better. Also, if they develop a serious illness or a serious adverse event related to the study, allocated interventions will discontinue. Participants can continue to receive health counseling services from clinicians after completing the study. Doctors should offer alternative treatments for patients who have completed the trial without remission, such as combined conservative treatments like acupuncture.

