### Assessment of safety

All unexpected or unfavorable events affecting patients in the study, such as heavy menstrual flow, nausea, bloating, diarrhea, and stomach upset, associated with treatment [18, 19], will be recorded in detail in the CRFs and followed up for the duration of the study. Investigators will confirm the relatedness of adverse events and treatment and report treatment-related adverse events. In case of adverse reactions, the clinical observer can decide whether to stop the trial depending on the patient’s condition. In the event of any serious adverse events (SAEs), emergency medical assistance will be sought. The outcome will be assessed at 1, 2, and 3 months after randomization.

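### Efficacy and safety are both evaluated on the FAS and a completers-only per-protocol set, with neither named primary; the per-protocol set should not be used for safety, and the adverse-event schedule needs reconciling

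*Protocol article*

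**What the plan says.** Data analysis: "Both the full analysis set (FAS) and the per-protocol analysis set (PPS) will be used simultaneously to evaluate the effect and safety of GFW". The two sets are then defined: "The FAS is for all participants who complete randomization and are assigned to receive treatment", and "The PPS is for the individuals who receive the assigned treatment according to the protocol and complete the entire study". Neither is called primary, nothing is said about discordant results, and no separate safety set is defined. The same section promises a descriptive summary of adverse events without limiting it to related ones.

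Interventions gives two ways of leaving the planned course. Participants may withdraw if they feel no improvement, and "if they develop a serious illness or a serious adverse event related to the study, allocated interventions will discontinue". Assessment of safety adds that the clinical observer may decide to stop after an adverse reaction, depending on the patient's condition.

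Assessment of safety also covers what is recorded and when. It starts broadly with "All unexpected or unfavorable events affecting patients in the study", although the same sentence goes on to speak of association with treatment, and it has events followed throughout the study. It then says "Investigators will confirm the relatedness of adverse events and treatment and report treatment-related adverse events", and "The outcome will be assessed at 1, 2, and 3 months after randomization". Outcome measurements schedules all outcomes at baseline and months 1 to 6. Data collection and management has assessors completing case report forms at each visit, with visits running to month 6.

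**The concern.** A per-protocol set defined by adherence and completion is conditioned on what happens after randomisation. For safety this is the wrong condition: patients who could not tolerate the treatment are those least likely to qualify. Given equal standing beside the FAS, the per-protocol display can be quoted as the safety profile of GFW while lacking the patients of most interest.

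For efficacy, two sets of equal rank and no rule for disagreement leave the choice of headline result open until both are known. Because participants who feel no better may leave, the per-protocol comparison is also no longer protected by randomisation.

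The adverse-event text matters for the same reason. If a reader of the protocol takes the relatedness sentence or the month 1 to 3 sentence as the governing rule, the adverse-event data will be narrower than the rest of the article implies. Relatedness is a judgement, and the Discussion concedes slight differences in odour and taste between the granules, so that judgement may not be fully blind.

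**Working it through.** The article gives no figure for this point. Its sample size supplies two inputs: 64 per arm, and 10% dropout, which is 0.10 × 64 = 6.4, or about 6 patients per arm. That leaves 58.

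**1. Who can appear in each set.**

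| Patient | FAS | Per-protocol set |
|---|---|---|
| Treatment stopped for a related serious adverse event | included | excluded (planned course not received) |
| Withdraws because of poor tolerability | included | excluded (study not completed) |
| Withdraws because of no improvement | included | excluded (study not completed) |
| Adverse event, but finishes course and follow-up | included | included |

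The first row takes treatment according to the protocol to mean the planned course. On that reading, the per-protocol rate of related serious events that stop treatment is zero whatever the true rate. This covers only events that stop treatment. Milder events in patients who carry on are counted in both sets.

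**2. How far the safety rate can move.** The event counts are assumed, because the article gives none. Take one arm of 64 with 6 dropouts.

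| Patients with an event in FAS | FAS rate | Per-protocol, 3 dropouts due to events | Per-protocol, 6 dropouts due to events |
|---|---|---|---|
| 6 | 6/64 = 9.4% | 3/58 = 5.2% | 0/58 = 0% |
| 10 | 10/64 = 15.6% | 7/58 = 12.1% | 4/58 = 6.9% |
| 13 | 13/64 = 20.3% | 10/58 = 17.2% | 7/58 = 12.1% |

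If no dropout had an event, the per-protocol rate would be slightly higher than the FAS rate (10/58 = 17.2% against 15.6%). The understatement therefore depends on dropouts having events more often than those who stay, which the stopping provisions make likely.

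**3. Efficacy, if either set could carry the claim.** Assume one test per set at two-sided 0.05, no true effect, and a per-protocol set that is a random fraction f of the FAS. The two test statistics then have correlation √f, and the chance that at least one is significant is 1 − P(|Z₁| < 1.96 and |Z₂| < 1.96). The simulation used t-tests with 64 per arm and 40,000 replicates.

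| f | √f | Either significant | Simulation, either | Simulation, both |
|---|---|---|---|---|
| 0.90 | 0.949 | 0.065 | 0.067 | 0.037 |
| 0.80 | 0.894 | 0.071 | 0.070 | 0.030 |
| 0.70 | 0.837 | 0.076 | 0.076 | 0.025 |

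Two independent tests would give 1 − 0.95² = 0.0975, so nesting keeps the inflation well below that ceiling. Requiring both sets to be significant takes the error below 0.05. The figures do not include selection bias, because they assume random exclusion.

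**4. Adverse-event text side by side.** Following events for the whole study, and visits to month 6, cannot both stand unqualified beside an assessment at months 1, 2 and 3 only. An unrestricted descriptive summary of adverse events does not sit easily beside a sentence that names treatment-related events as what is reported.

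**The case against.** The strongest reply is that the FAS sits next to the per-protocol set and loses nobody. A reader might infer that harms leading to withdrawal vanish from the trial's results. They do not: every such patient remains in the FAS, and only the per-protocol display is affected.

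A reader might also infer that only related events are reported and that safety data stop at month 3. The documents do not support that either. Recording begins from a broad statement, events are followed throughout the study, and the adverse-event summary carries no relatedness filter. What stands is an inconsistency.

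It is tempting to add that the third course may end after the month 3 assessment. That depends on the cycle day of randomisation, which the article does not fix. With 35-day cycles and month 3 at day 91, randomisation at cycle start puts the last dose near day 107 (16 days after). Randomisation 7 days before menses puts it near day 79 (12 days before). No figure for a gap can be drawn from this.

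On efficacy, the article does not say that success in either set is enough, and a rule requiring both would be conservative. Nor can it be said that the per-protocol set favours GFW: if more non-improvers leave the placebo arm, their removal flatters placebo. Naming a primary set is often left to the analysis plan, and the trial calls itself exploratory. Those points limit the weight of the efficacy part. They do not answer the safety part, because using a completers-only set for safety is a rule the article states, not a detail it defers. The Discussion also presents the trial as a source of reliable evidence on efficacy and safety.

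**Conclusion.** The point holds in a limited form and should be corrected before unblinding.

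- **Safety:** the per-protocol result leaves out patients who stop because of harm, while the FAS keeps them. In the assumed example with 10 events in the FAS, the rate falls from 15.6% to between 12.1% and 6.9% when three to six of the six dropouts are due to events.
- **Efficacy:** the per-protocol result is selected on outcome after randomisation, in a direction that is not known. Type I error would be about 0.065 to 0.076 only if significance in either set were accepted, with assumed per-protocol fractions of 90% to 70% and random exclusion.
- **Adverse-event scope and timing:** the statements conflict and must be reconciled. They do not establish that safety data are cut off at month 3 or confined to related events.

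**What to change.** 1. Name the FAS, all randomised participants analysed as assigned, as the sole primary efficacy set. Keep the per-protocol set as supportive, with the conclusion resting on the FAS if the two disagree.
2. Remove the per-protocol set from the safety analysis. Define a safety set of all participants who took at least one dose, analysed by treatment received.
3. Tabulate all recorded adverse events by arm, with investigator-judged relatedness as a secondary column.
4. Reconcile Assessment of safety with itself, with Outcome measurements and with Data collection and management, so that one statement governs when adverse events are assessed. They can be recorded at the visits already held to month 6.

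The cost is a wording change in the protocol and analysis plan, plus one adverse-event form at three existing visits (months 4, 5 and 6). Sample size, randomisation and treatment are unaffected.

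### LOCF is the only missing-data method, yet the primary outcome lies three months after treatment ends; if the effect wanes, carried-forward scores bias the month-6 difference

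*Protocol article*

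**What the plan says.** Five statements in the protocol article bear on this point.

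- **Data analysis**, on missing values: "For missing data, we will use the last-observation-carried-forward method". No other method and no sensitivity analysis is named.
- **Design and setting**, on the timeline: "a 1-month baseline period, a 3-month treatment period, and a 3-month follow-up period".
- **Primary outcome**: "The primary outcome is the mean menstrual pain intensity change measured by visual analog scale (VAS) from baseline to 6 months". The end point of that interval falls three months after treatment has stopped.
- **Interventions**, on leaving: "Participants are free to withdraw from the trial if they feel they are not getting better".
- **Sample size**, on losses: "Considering an estimated 10% dropout rate", the target rises from 116 to 128 patients.

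The outcomes are to be analysed by repeated-measures ANOVA or GEE, with the choice left open. On analysis sets: "Both the full analysis set (FAS) and the per-protocol analysis set (PPS) will be used simultaneously". The per-protocol set is limited to those treated according to protocol who finish the whole study.

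**The concern.** LOCF assumes that a participant's pain stays at its last recorded level. The schedule gives no ground for that assumption, because treatment stops at month 3 and the primary outcome is read at month 6. Someone last seen at month 3 enters month 6 with a score from the treatment period, and someone last seen at month 1 enters with an early one. If the benefit of GFW fades after treatment stops, copied month-3 scores can make it seem to last.

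The stated freedom to withdraw for lack of improvement makes outcome-dependent losses plausible. If GFW works during treatment, such losses would be more frequent on placebo, and poor scores would be frozen there.

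This is a method the article fixes, not a detail it leaves to an analysis plan. Nothing else in the plan would reveal the problem. The per-protocol set leaves out the people whose scores are carried forward, so it is a completer analysis and does not test the LOCF assumption.

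**Working it through.** **Inputs from the Sample size section.** "a mean difference of 1 between two groups, SD of total score of 1.67"; power 0.9; 58 per arm before dropout; 10% dropout; 64 per arm after it.

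**The plan's own figure.** n per arm = 2 x (1.960 + 1.282)^2 x 1.67^2 / 1^2 = 2 x 10.507 x 2.789 = 58.6. The stated 58 per arm (116) follows at two-sided 0.05, apart from rounding up to 59. The literal two-sided 0.025 gives 69.2, or 70 per arm. That is a separate matter, as is the scale: 1 and 1.67 look like 0-10 units although the VAS is scored 0 to 100. Results below are in the plan's units and are best read as fractions of the planned difference.

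**What LOCF estimates.** Let D3 and D6 be the true group differences at months 3 and 6, and d the fraction of each arm last seen at month 3, lost at random:

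LOCF difference = (1-d) x D6 + d x D3, so bias = d x (D3 - D6).

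With D3 = 1 (assumed equal to the planned difference):

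| True D6 | LOCF, d = 10% | LOCF, d = 20% |
|---|---|---|
| 1 (sustained) | 1.00 | 1.00 |
| 0.5 (half waned) | 0.55 | 0.60 |
| 0 (fully waned) | 0.10 | 0.20 |

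**Effect on type I error when D6 = 0.** SE = 1.67 x sqrt(2/64) = 0.295. A bias of 0.10 is 0.10/0.295 = 0.34 standard errors. The two-sided rejection rate is then Φ(-1.96 + 0.34) + Φ(-1.96 - 0.34) = 0.053 + 0.011, about 6.3%.

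**Simulation.** 4000 trials, 64 per arm, SD 1.67, month-6 two-sample test. Assumed: correlation 0.6 between visits, and dropouts last seen at month 3.

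| Scenario | Dropout GFW / placebo | LOCF estimate | Rejection |
|---|---|---|---|
| D6 = 0, random | 10% / 10% | 0.10 | 6.3% |
| D6 = 0, poor responders leave | 11% / 17% | 0.14 | 8.1% |
| D6 = 0, random | 20% / 20% | 0.20 | 10.0% |
| D6 = 0, poor responders leave | 20% / 29% | 0.22 | 12.4% |
| D6 = 1, flat after month 3 | 10-11% / 10-17% | 1.00-1.04 | not applicable |

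In the second row the complete data of the same runs averaged 0.010 and not 0, so the bias net of simulation noise is 0.141 - 0.010 = 0.13. By the formula above that gives about 7.2% rejection. The range of 6 to 8% covers both.

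**If the contrast averages over all six visits.** Take true differences of 1, 1, 1, 0.67, 0.33, 0 and 10% random loss after month 3. Only months 4 to 6 are affected: 0.1 x (0.33 + 0.67 + 1)/6 = 0.03.

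**Precision.** Under the same correlation, three observed visits explain 3 x 0.36/(1 + 2 x 0.6) = 0.49 of the month-6 variance. A likelihood analysis with 10% lost then has SE 0.295 x sqrt(0.51/0.9 + 0.49) = 0.303, about 3% larger. At 20% lost it is 0.313, about 6% larger.

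**The case against.** The strongest reply is that the bias may never arise. The Interventions section permits withdrawal for lack of improvement but does not forecast it. The Sample size section gives one dropout figure with no difference between arms, and the Data collection and management section lists retention measures. No passage says how pain will behave after treatment stops; with a flat profile the bias is essentially nil. The primary outcome wording can also be read as a comparison over all visits, where the bias is about 0.03. The trial calls itself exploratory. All of this stands, and it limits the size of the point. It does not justify LOCF, because the plan cannot know beforehand that the profile will be flat and has no analysis that would show otherwise.

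Three stronger readings are tempting and are not supported.

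- *LOCF favours GFW even if GFW does nothing.* If GFW has no effect at any time and blinding holds, both arms have the same outcomes and the same response-driven dropout. The carried-forward scores are then exchangeable between arms, the expected bias is zero and type I error stays at its nominal level. The inflation shown above needs an effect during treatment that has gone by month 6.
- *LOCF seriously understates the standard error.* In the simulation the LOCF standard error matched the estimator's own sampling spread. Its shortfall against a valid analysis that assumes data missing at random is about 3% at 10% dropout. Bias is the main harm.
- *The plan's GEE option already solves this.* The text does not say that GEE would be run without LOCF. Unweighted GEE on incomplete records needs data missing completely at random, so it would not be safe under response-driven dropout either.

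**Conclusion.** The point holds as a conditional bias that should be removed; it does not invalidate the trial. A single imputation rule, with no sensitivity analysis, can put on-treatment or early scores in place of off-treatment month-6 scores.

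At roughly the planned dropout, a month-3 difference of 1 that has fully waned would appear at month 6 as about 0.10 to 0.14, or 10 to 14% of the planned difference. Type I error at month 6 would be about 6 to 8%. These figures rest on assumptions the article does not supply: full waning, correlation 0.6, last contact at month 3, and a month-6 contrast. Half waning roughly halves the bias, averaging over visits cuts it to about 0.03, and a flat profile removes nearly all of it. Dropout near 20% roughly doubles it.

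Confidence is high that LOCF is the sole stated method and is ill-suited to this timeline. It is lower on the size and direction of the bias in the trial itself.

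**What to change.** Replace the LOCF sentence in Data analysis with:

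> The primary analysis is a likelihood-based mixed model for repeated measures on all observed VAS data, without single imputation, with the group difference at month 6 as the contrast. A sensitivity analysis uses multiple imputation with a delta or reference-based adjustment for participants who withdraw for lack of improvement.

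The model uses the monthly assessments already planned and is valid when dropout depends on scores already recorded. The sensitivity analysis covers dropout that depends on what was not recorded. Naming the month-6 contrast also settles whether the primary comparison is at month 6 or averaged over visits.

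In addition, continue the existing VAS diaries to month 6 for participants who stop study treatment and still agree to follow-up. This reduces missing data at source and changes no treatment rule.

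Cost: wording, some extra programming, and a standard error about 3% larger at 10% dropout. The planned sample size need not change for this point. The article reports that recruitment was under way, so the change should be documented before unblinding.
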